### Study population (inclusion and exclusion criteria)

The targeted study population includes all patients scheduled for elective open PD (Whipple or pylorus-preserving) with reconstruction using a pancreatojejunostomy (anastomosis of the pancreas to the jejunum) in cases of tumors or cystic lesions of the pancreatic head, the distal bile duct, and the duodenum or in cases of chronic pancreatitis. Further inclusion criteria are as follows: male and female patients, age equal to or older than 18 years, American Society of Anesthesiologists (ASA) score I–III, and a completed written informed consent form. Exclusion criteria are as follows: potential conditions/circumstances after previous abdominal surgery with resection of the falciform ligament (e.g., status post liver resection), no creation of a pancreatojejunostomy (e.g., pancreatogastrostomy, total pancreatectomy, or non-resectability), and simultaneous arterial resection or reconstruction (e.g., hepatic or splenic, or superior mesenteric artery).

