### Surgical technique

The standard technique of PD and surgical instruments may vary in several aspects. The technique and critical steps of the own Dresden center were described elsewhere [15].

The following operation steps are crucial for the trial evaluation and are predefined for patients in both the intervention and control arms:The abdominal incision can be either a midline laparotomy or a transverse subcostal incision.After opening the abdominal cavity, attention should be paid to preserve the round and falciform ligament over its entire length, before division near the umbilicus and separation from the ventral abdominal wall.Preparation of the falciform ligament (see also [12]): The falciform ligament is then further dissected from the ventral abdominal cephalad along the ventral attachment. At the junction to the coronary ligament, the falciform ligament is freed from the ventral hepatic surface until the round ligament is reached. This technique results in a pedicled falciform ligament, with the round ligament being the pedicle.When dividing the GDA, the stump of the GDA should be kept as long as possible. Division of the GDA is performed using a suture stitch (Prolene 4-0) and two titanium clips as a standard. Other deviating techniques of dividing the GDA are allowed according to the protocol but should be recorded in the case report form (CRF).Reconstruction is achieved by an end-to-side pancreatojejunostomy. The technique of this type of anastomosis is at the discretion of the surgeon.A resection of the portal vein can be performed if necessary and is no exclusion criterion.Intra-abdominal drains can be placed after completion of the operation.

For patients in the intervention group, the technique for creation of the pedicled falciform ligament wrap as it should be performed in this trial is as follows: After completion of the pancreatic, bile duct, or gastric/duodenal anastomosis, the prepared pedicled falciform ligament is carefully tunneled below the common HA and wrapped around the GDA stump in a tension-free fashion using only one turn. Fixation is then performed with two to three stitches using polydioxanone (PDS) 5-0. The last step is to ensure a proper pulsation of the HA after completion of the wrap. The covering of the divided and skeletonized arteries (GDA stump, hepatic artery) by the pedicled falciform ligament patch is a quick and safe surgical procedure for experienced pancreatic surgeons.

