### Randomization

Patients will be screened for eligibility considering the inclusion criteria (see above) on the day of admission (usually the day before the surgery). After obtaining the written informed consent, the randomization will be performed intraoperatively after proving the exclusion criteria. The randomization is designed as block randomization (via envelopes), with fixed block sizes in a 1:1 allocation ratio. The envelopes were prepared by an authorized trial coordinator at the center in Dresden and distributed to the participating sites as needed. It is mandatory to check all eligibility criteria before opening of a randomization envelope by authorized trial personnel only. The investigator has to consecutively assign the envelopes to the patients. He is requested to document the assignment carefully in the patient identification log.

The details of the randomization will be kept safe and confidential. Subjects withdrawn from the trial retain their identification codes (e.g., randomization number). New subjects receive a new identification code.

The randomization sequence was generated using the established R statistics software package (R version 3.1.3, the R Foundation for Statistical Computing). The block size will be kept confidential until completion of recruitment. Eligible patients will be randomized intraoperatively to one of the two groups (control group or intervention group) after the surgeon has confirmed resectability and the availability of the pedicled falciform ligament. In cases when exclusion criteria (e.g., no performance of a pancreatojejunostomy or total pancreatectomy) are met after randomization, the respective patients were withdrawn from the trial.

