### Statistical considerations and sample size calculation

A comprehensive systematic literature review was performed and published by the authors in advance [12]. As a result, no prospective studies were identified which investigated a prophylactic round or falciform ligament wrap on the GDA stump for prevention of PPH. One retrospective study with a historical control group showed a significant reduction of postpancreatectomy bleeding by covering with an omental flap (*p* = 0.021; OR = 0.151; 95% CI, 0.030–0.751 [16]). The best available data on the falciform ligament wrap comes from China and was published in 2014. Xu et al. recently published a retrospective controlled review involving 140 patients per group, using the falciform ligament wrap as preventive intervention to reduce erosion hemorrhage [17]. There was one event in the intervention group, compared with nine events in the control group (incidence, 0.7 vs. 6.4%). The incidence of 6.4% seemed high, but an in-depth analysis of the own cohort supported that incidence [12]. The sample size estimation for the present trial was therefore based on the reduction of erosion hemorrhage rate from 6.4 to 0.7%. We used a two-tailed Fisher exact test for sample size calculation. To achieve an 80% power with a two-sided *p* value of less than 0.05, a group size of 174 patients is required. With a drop-out rate of 13%, the total sample size was calculated at 400 patients with 200 in each of the two groups.

Statistical analysis will be performed on an intention-to-treat and on a per-protocol-principle analysis. The Fisher exact test will be used to compare the different incidences of the primary and secondary endpoints. Statistical significance will be set at 0.05. The Student *t* test will be used to compare continuous variables (e.g., operation time), or alternatively the Mann-Whitney test. Statistical calculation will be done using the R statistics software package (R version 3.1.3, the R Foundation for Statistical Computing). The study protocol defines no interim analysis.

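### Withdrawing randomized patients who turn out to have no pancreatojejunostomy conflicts with the promised intention-to-treat analysis and may bias the comparison

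*Protocol article*

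**What the plan says.** The Randomization section of the protocol article sets two conditions on allocation. First, "It is mandatory to check all eligibility criteria before opening of a randomization envelope". Second, patients are randomized during the operation "after the surgeon has confirmed resectability and the availability of the pedicled falciform ligament". The same section then provides for exclusion criteria that surface later. It names a reconstruction without pancreatojejunostomy and total pancreatectomy as examples, and says that if such criteria "are met after randomization, the respective patients were withdrawn from the trial". Withdrawn patients keep their identification code. The article does not say that they are followed to 3 months or analysed.

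Under the study population, failure to create a pancreatojejunostomy is an exclusion criterion, with pancreatogastrostomy, total pancreatectomy and non-resectability as examples. Under surgical technique, the wrap is made "After completion of the pancreatic, bile duct, or gastric/duodenal anastomosis".

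The statistical section states: "Statistical analysis will be performed on an intention-to-treat and on a per-protocol-principle analysis".

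**The concern.** An ITT analysis keeps every randomized patient in the allocated arm, whatever happens afterwards. A rule that takes randomized patients out of the trial because of an event after allocation produces a different set, so the withdrawal sentence and the ITT promise cannot both be carried out as written.

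The criteria at issue are not baseline facts discovered late. Whether a pancreatojejunostomy is made is decided during the operation, and that decision can come after the envelope has been opened. The article links erosion hemorrhage to pancreatic fistula and soft pancreatic tissue. A reconstruction choice that depends on the state of the gland is therefore plausibly related to the primary endpoint. If such choices also differed between arms, the remaining patients would no longer be comparable.

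There is also a practical loss. If withdrawal ends data collection, no later analysis plan can restore the missing 3-month outcomes. The article reports recruitment as ongoing.

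**Working it through.** **1. Sequence of events.** From the Randomization and Surgical technique sections:
- resectability and ligament availability are confirmed;
- the envelope is opened;
- the anastomoses are completed;
- the wrap is made in the intervention arm.

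Allocation is not tied to a completed pancreatojejunostomy. The check before the envelope is opened cannot verify a reconstruction that has not yet been made, and the withdrawal sentence itself recognises this. Nothing in the article withholds the arm from the surgeon until the anastomosis is done.

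**2. The plan's own figure.** Inputs from the statistical section: 6.4% versus 0.7%, two-sided Fisher exact test at 0.05, 80% power, 13% drop-out. Power is the sum, over all pairs of event counts (a, b), of Bin(a; n, 0.064) × Bin(b; n, 0.007) for pairs with Fisher p < 0.05.
- n = 173 per arm: 79.7%
- n = 174 per arm: 80.0%
- 174 / (1 − 0.13) = 200 per arm, 400 in total

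The sample size reproduces and is not in question.

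**3. What could go wrong without the fix.** This is an illustration, because the documents give no number or risk for withdrawn patients. Assumptions: no true effect, 6.4% in both arms, 200 randomized per arm, and w patients with event risk r withdrawn from the wrap arm only. The rate among retained wrap patients is (200 × 0.064 − w × r) / (200 − w). For w = 20 and r = 0.15 this is (12.8 − 3.0) / 180 = 5.44%. The chance of a significant result in favour of the wrap is then:

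| Withdrawn, wrap arm only | r = 6.4% | r = 15% | r = 30% |
|---|---|---|---|
| 0 | 1.5% | – | – |
| 10 | 2.1% | 3.2% | 6.3% |
| 20 | 1.8% | 4.3% | 17.1% |

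When withdrawal is unrelated to risk, the error stays near 2%. Marked inflation needs withdrawal that is both selective for risk and unequal between arms.

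**4. Price of the fix.** Keep all 200 per arm with complete outcomes, and let a share d of each arm have no pancreatojejunostomy. Two assumptions bracket their risk:
- control risk without wrap benefit: control 0.064; wrap (1 − d) × 0.007 + d × 0.064. At d = 4% the wrap rate is 0.00672 + 0.00256 = 0.00928.
- no risk: both planned rates multiplied by (1 − d).

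| d per arm | Power, control risk | Power, no risk |
|---|---|---|
| 0% | 86.7% | 86.7% |
| 2% | 83.8% | 85.8% |
| 4% | 80.9% | 84.9% |
| 5% | 79.3% | 84.4% |
| 10% | 71.4% | 81.7% |

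**5. Sensitivity of the test.** Expected events at 174 per arm are 0.064 × 174 = 11.1 and 0.007 × 174 = 1.2. For 1 versus 11 events, Fisher p = 0.0055. With 1 event in the wrap arm, 8 control events give p = 0.037 and 7 give p = 0.067. At the planned rates the verdict does not hang on one event; it does only when the observed table lies near the boundary.

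**The case against.** Several points on the other side stand. Eligibility must be checked before the envelope is opened, and the visit schedule repeats the exclusion check on the day of operation, so late exclusions may be rare. The withdrawal rule applies to both arms alike. The wrap follows the anastomoses and concerns the artery stump, and no text suggests that allocation influences whether a pancreatojejunostomy is made. After a total pancreatectomy there is no pancreatic anastomosis to leak, so those removals would plausibly take few events with them. Bias that depends on the arm is therefore possible but not shown. A full protocol or analysis plan that is not shown may also define the ITT set.

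These points limit the size of the harm. They do not remove the conflict, because the article states a positive rule that removes randomized patients and no text keeps their outcomes.

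A reader might be tempted to go further in three ways, none of which the article supports:
- **Reading the 13% allowance (26 of 200 per arm) as the number of such withdrawals.** It is a general drop-out allowance, and the article gives no count of these cases.
- **Claiming that keeping everyone costs no planned power.** The 86.7% assumes complete outcomes and undiluted risks. Under the control-risk assumption, power is already just below 80% at a 5% share.
- **Treating the lack of a stated order between the ITT and per-protocol analyses as an error.** An analysis plan commonly settles this, and that plan is not shown.

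**Conclusion.** The point holds in a limited form. The withdrawal rule and the ITT promise contradict each other as written, and the analysis set that the rule produces is not ITT. The primary comparison may be biased, because the excluding decision can follow allocation, may be made with the arm known, and plausibly relates to bleeding risk. The size and direction of any bias cannot be determined from the article. Bias is small if such withdrawals are few and unrelated to arm or risk, and it becomes material only if they are selective and unequal between arms. Removing the conflict is affordable: under the less favourable of the two dilution assumptions, power stays at or above 80% while these cases make up no more than about 4% of each arm, provided outcomes are complete.

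**What to change.** Replace the withdrawal sentence in the Randomization section with a rule to this effect: every randomized patient remains in the trial, is followed to 3 months and is analysed in the allocated arm in the ITT set, whatever reconstruction was performed; patients without a pancreatojejunostomy leave the per-protocol set only. Report these cases by arm with reasons. For patients already withdrawn, retrieve the 3-month outcome where consent allows.

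The cost is one amended sentence, the 3-month follow-up of these patients, and some dilution of the effect. Their number is not known from the article, so the trial team should count them by arm now and read the loss of power from the table above.

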### Study visits and data collection

The trial includes a total of five study visits during the operation or the postoperative period. The period ranges from the day of the operation until 3 months after the operation (Table 1). All outcome parameters will be recorded by a surgical resident or fellow before and after the operation, i.e., on postoperative days (POD) 3 and 10 and on the day of discharge. After 3 months postsurgery, a follow-up examination is scheduled on an outpatient basis. During each visit at the delineated endpoints, the patient characteristics will be collected and recorded according to the CRF.

**Table 1 Tab1:** Visit schedule

	Study period					
	Screening day of admission	Day of operation	POD 3	POD 10	Day of discharge	3 months after operation
Inclusion criteria	X					
Exclusion criteria	X	X				
Patient characteristics	X					
Randomization		X				
Used surgical technique		X				
Laboratory tests Morbidity			X	X	X	X

The study will collect baseline demographic data and information regarding the disease course (e.g., neoadjuvant therapy) and comorbidities from the included patients. During the postoperative study visits, routine blood tests (including hemoglobin concentration, leukocyte count, serum C-reactive protein, bilirubin, and liver and pancreatic enzymes) will be screened. Further, the amylase concentration in abdominal drains on the respective postoperative day (POD 3 and 10 or on the day of an intervention, e.g., CT-guided drainage) is recorded for identification and grading of a POPF. If no abdominal drains were inserted intraoperatively, the grading of a POPF is confined to the clinically relevant grades B and C (secondary endpoint) depending on the respective intervention or clinical status of the patient.

According to protocol, a CT scan of the abdomen or a CT angiography is not routinely performed during the study period. These diagnostic exams are indicated by the responsible physicians in each of the participating centers based on a medical rationale (e.g., suspected intra-abdominal fluid collection or hemorrhage, elevated liver enzymes or white blood cells/serum C-reactive protein). This management is considered standard in a certified pancreatic center. Further, symptomatic cardiorespiratory complications (e.g., pneumonia or myocardial infarction) are recorded based on routine diagnostic tests.

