### Aim of the study and study endpoints

The aim of the study is to evaluate whether a pedicled falciform ligament wrap can decrease erosion hemorrhage of the stump of the GDA in the presence of a POPF.

Therefore, the primary endpoint of the study is the rate of postoperative erosion hemorrhage from the GDA stump or the HA within 3 months from the index operation.

The secondary endpoints are:Incidence of late PPH (according to the International Study Group of Pancreatic Surgery (ISGPS) definition [13]) in the entire study population and divided into subgroups with soft and hard pancreatic texture (also depending on the underlying histopathology [e.g., cancer, cystic lesion, or chronic pancreatitis])Incidence of clinically relevant POPF (according to POPF grades B and C, ISGPS definition [3, 14])Incidence of symptomatic hepatic malperfusion and narrowing/stenosis of the HA (diagnosed by computed tomography or angiography)Postoperative rate of therapeutic interventions (computed tomography-guided drainage or angiographic studies)Reoperation ratePostoperative morbidity and mortality (during hospital stay and at 3 months postoperative)

Erosion hemorrhage from the GDA stump or the HA is defined as postoperative bleeding or pseudoaneurysm formation (proved by CT angiography, conventional angiography, or relaparotomy) from the GDA stump or the HA within 3 months from the index operation. Clinically relevant POPF grade C is defined as POPF, which is causative for a reoperation, organ failure, or death of the patient [14].

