## Discussion

The clinical trial is the first randomized controlled study to investigate the effectiveness of a pedicled falciform ligament wrap for prevention of postpancreatectomy erosion hemorrhage. Creation of a falciform ligament wrap is a simple surgical technique with low associated morbidity. In the past, the falciform ligament has been used in hepatic injury [18] or for perforated duodenal ulcer [19]. More recently, it has been assessed for prevention of POPF after distal pancreatic resections [20]. The latter technique is at present analyzed by the randomized, controlled “DISCOVER” trial [21].

Compared with POPF, delayed erosion hemorrhage occurs less frequently but carries a high mortality [22]. The substantial mortality is closely related to the incidence of a POPF, formation of a pseudoaneurysm, delayed PPH, and soft pancreatic tissue [23]. Furthermore, pseudoaneurysm formation of the visceral vessels may be favored by the radicality of vascular dissection and lymphadenectomy, as well as by the length and closure of the GDA stump.

Before initiating the present trial, we performed a retrospective analysis of our own experience in using the pedicled falciform ligament wrap for patients undergoing PD. The study confirmed the high mortality of erosion hemorrhage (39%) and the feasibility of the technique. However, only 39 patients with the wrap were retrospectively identified, and the difference compared with cases without the wrap was not significant [12]. We then continued with a systematic literature review and found that the overall reported rate of erosion hemorrhage after PD and pedicled falciform ligament wrap is low (0.9%). In comparison, the median rate of erosion hemorrhage in studies which reported outcomes of PDs without the use of a wrap was 4.1 (interquartile range, 3.7–4.7) [8, 9, 23, 24].

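### The primary event counts only if proved by discretionary imaging or relaparotomy, so an unproven fatal bleed is a non-event and a silent pseudoaneurysm counts only where someone looked

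*Protocol article*

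**What the plan says.** Under *Aim of the study and study endpoints*, erosion hemorrhage from the GDA stump or hepatic artery within 3 months "is defined as postoperative bleeding or pseudoaneurysm formation", and it must be "proved by CT angiography, conventional angiography, or relaparotomy". These are the only accepted proofs; autopsy is not among them.

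Under *Study visits and data collection*, "a CT scan of the abdomen or a CT angiography is not routinely performed during the study period". The decision is local: "These diagnostic exams are indicated by the responsible physicians in each of the participating centers based on a medical rationale". The triggers are given as examples without thresholds: "suspected intra-abdominal fluid collection or hemorrhage, elevated liver enzymes or white blood cells/serum C-reactive protein". On recording, the same section says: "All outcome parameters will be recorded by a surgical resident or fellow".

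Under *Randomization*, allocation takes place during the operation, so the team that makes or omits the wrap knows the arm. The confidentiality wording there concerns the randomization details and the block size. The article describes no masking of treating physicians or of those who record outcomes.

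**The concern.** Two kinds of case depend on whether someone looked.

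- **Fatal bleed without proof.** A patient who dies of a bleed from the GDA stump or hepatic artery before CT angiography, angiography or relaparotomy does not meet the definition. Autopsy evidence of the source would not change that. A death of the kind the trial hopes to prevent would then be counted with the patients free of the event.
- **Silent pseudoaneurysm.** This is an event only in a patient who was scanned or reoperated on for some reason. If the arms are scanned at different rates, for example because knowledge of the wrap changes the level of suspicion, the observed rates can differ with no true difference.

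The trial rests on very few events, so a handful of such cases could change its conclusion.

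**Working it through.** **Inputs** (*Statistical considerations and sample size calculation*): 6.4% control, 0.7% wrap, two-sided Fisher exact test at 0.05, 80% power, 174 per group, 13% drop-out, 200 per group.

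**Step 1: reproduce the plan's figure.** Exact power is the sum, over all pairs of event counts (a, b) with Fisher p<0.05, of Bin(a; n, 0.064) × Bin(b; n, 0.007).

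- n=173 gives 79.7%; n=174 gives 80.0%.
- 174 / (1 − 0.13) = 200 per group.

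The sample size is correct. The issue is how events are ascertained.

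**Step 2: expected events at 174 per arm.**

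- Control: 174 × 0.064 = 11.1
- Wrap: 174 × 0.007 = 1.2

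**Step 3: how far one case moves the result** (two-sided Fisher, 174 per arm).

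| Control vs wrap events | p |
|---|---|
| 11 vs 1 | 0.006 |
| 11 vs 2 | 0.020 |
| 11 vs 3 | 0.052 |
| 8 vs 1 | 0.037 |
| 7 vs 1 | 0.067 |

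From 11 vs 2, one more wrap event removes significance. From 8 vs 1, one fewer control event does the same. From the expected 11 vs 1, it takes two more wrap events.

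**Step 4: unequal detection with no true effect.** The documents give no scanning or detection rates, so these are assumptions: a true rate of 4% in both arms, and extra detected events in controls only. The rejection probability is computed as in Step 1.

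| Extra points in controls | Extra patients per 174 | Observed rates | Rejection probability |
|---|---|---|---|
| 0 | 0 | 4% vs 4% | 2.4% |
| 0.5 | 174 × 0.005 = 0.9 | 4.5% vs 4% | 2.8% |
| 1 | 174 × 0.01 = 1.7 | 5% vs 4% | 4.0% |
| 2 | 174 × 0.02 = 3.5 | 6% vs 4% | 8.7% |
| 3 | 174 × 0.03 = 5.2 | 7% vs 4% | 16.4% |

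Fisher's test is conservative here (2.4% with equal detection), so an excess of up to 1 point stays below the nominal 5%. An excess of 2 points or more does not.

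**The case against.** Much of the opposing case stands.

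- **Unproven fatal bleeds should be uncommon.** *Trial design and study setting* requires immediate CT access and 24-hour interventional radiology at certified centers. Late hemorrhage, reoperation and mortality are secondary endpoints, and deaths are recorded as serious adverse events, so such a patient is not lost to the trial. The primary comparison would still count that patient as a non-event.
- **The 39% mortality does not measure the problem.** A reader might infer that a large share of events goes uncounted. The figure in the *Discussion* is mortality after erosion hemorrhage in the retrospective cohort, not the share who die before proof. The Abstract gives over 30% and the *Background* 16–20%, and neither measures that share.
- **A loss of power cannot be claimed.** If 10%, 20% or 30% of events were missed in both arms, power would be 74.0%, 66.5% or 57.2%. But 6.4% and 0.7% are rates observed in a retrospective series. Reducing them further assumes that the series captured unproven deaths and that this trial will not, which nothing in the article supports.
- **Awareness of the arm is certain only for the operating team.** A reader might infer that those who order scans or record outcomes know it too. The article does not say, and the full protocol, which is not shown, may describe masking.
- **The direction of any bias is open.** Confidence in the wrap could reduce scanning in that arm. Concern about hepatic malperfusion, a secondary endpoint, with raised liver enzymes a listed trigger, could increase it.
- **Putting unproven clinical deaths into the primary event has a price.** It replaces objective proof with judgement, and one or two bleeds from another source could themselves decide the result. Such deaths therefore belong in a sensitivity analysis.

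None of this alters how the definition classifies these two kinds of case.

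**Conclusion.** The point holds as a gap in the primary endpoint definition, not as evidence of bias. As written, an unproven fatal bleed is a non-event even with autopsy evidence, and a silent pseudoaneurysm depends on a discretionary scan or a reoperation. The first consequence follows from the definition; the article states no separate rule for such deaths.

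The frequency of such cases is unknown and may be low. They matter because about 11 versus 1 events are expected, where one or two classifications can move the result across 0.05. The false-positive figures, 2.8% to 16.4% for 0.5 to 3 extra points against 2.4% with equal detection, illustrate an assumed one-sided excess. They do not predict its size or direction.

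The documents do not support the stronger claim that clinicians aware of the arm will systematically turn the worst outcomes into apparent successes and favour the wrap.

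**What to change.** 1. In the endpoint definition, add autopsy evidence of bleeding from the GDA stump or hepatic artery to the accepted proofs.
2. Pre-specify a sensitivity analysis of the primary endpoint that also counts death within 3 months with clinical hemorrhage and no other proven source.
3. Pre-specify a second sensitivity analysis restricted to clinically manifest bleeding, without incidental pseudoaneurysms.
4. Report by arm the number of patients who had CT, CT angiography or conventional angiography, so that readers can judge whether detection was comparable.

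The cost is one change of wording, two extra analyses and one table. No imaging or clinical management changes. The downside is that analysis 2 may include a few bleeds from another source, which is why it should not replace the primary analysis. The article reports recruitment as ongoing; these rules should be fixed before outcomes are examined by arm.

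Masked central classification of suspected cases is optional. It would need assessors who do not know the allocation, whom the article does not identify, and it could not correct for who was scanned.
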